### Methods

A first requirement is preoperative consent for HIPEC in gastrointestinal and gynecologic malignancy patients having abdominal-pelvic surgery for cancer (Tables 1, 2). Patients with a primary or recurrent cancer will require not only a standard consent for complete resection of the malignancy but also consent for HIPEC.The surgical procedure scheduled with the operating room must also include collection of the same day cytology specimen and possible administration of HIPEC. In order to avoid unnecessary delay, the equipment required for same day cytology must be available prior to the start of the surgical procedure. Also, the administration of the standard HIPEC for gastrointestinal or gynecologic malignancy must be possible with a few minutes notice.Collection of the same day cytology specimens: The same day cytology specimen is to be collected just after access to the abdomen and pelvis has been obtained (Fig. 1). Adhesions should be lysed to gain visual access to the right upper quadrant, right paracolic sulcus, left paracolic sulcus, and deep pelvis. An exploration of the abdomen and pelvis with a full description of the findings should be recorded in the operative note dictated by the surgeon. Prior to collection of the same day cytology specimen lysis of adhesions or surgical dissection that results in bleeding must be avoided. A bloody same day cytology specimen is more difficult to read. Also, blood contaminates the peritoneal fluid and will dilute the number of malignant cells identified.Four specimens of 50 ml each are to be obtained from each patient. If the patient has ascites no saline irrigation is required. Forcibly instill 50 ml into the right upper quadrant (superior and inferior to the liver), into the right paracolic sulcus, into the left paracolic sulcus, and into the deep pelvis posterior to the rectum. If the peritoneal fluid collection from each anatomic site is not equal to 50 ml, instill the volume of saline needed to provide a 50 ml specimen. The aspirations each containing 50 ml, should be contained in a suction container dedicated to the recovery of 200 ml of peritoneal fluid aspirate. It should leave the operating room table and be handed off to go to the cytology laboratory (800 cc Suction Canister, Cardinal Health Inc.).One of the assumptions of this phase 1 study is that a lavage of four anatomic sites at the time of the exploration of the abdomen and pelvis in a surgical procedure produces a higher likelihood of a positive result that a paracentesis. If same day cytology is available, it can simplify patient management and reduce the incidence of false negative peritoneal cytology.Preparation of the same day cytology specimen for the pathologist/cytologist: The 200 ml suction container is handed off the operating table, immediately uncapped and 500 units of heparin added. The 200 ml suction container is swirled to disperse the heparin. The 200 ml of peritoneal irrigation fluid or ascites are transferred to the Pathology/Cytology Department. Tubes containing the peritoneal fluid are centrifuged at 2000 rpm for 10 min. The fluid is suctioned off taking care to preserve the cellular pellet at the base of each tube. The cellular pellets from three tubes are agitated by pipette and transferred to the fourth tube. This tube is recapped, centrifuged, and transferred to the pathologist/cytologist for staining and reading.Staining and reading of the same day cytology specimen: A portion of the sediment is smeared on four glass slides. Two slides should be smeared with ~1 ml of sediment and prepared for microscope study by the Papanicolaou thin prep method. Two slides should be smeared with ~1 ml of sediment and allowed to air dry. They will be prepared for microscope study by the Diff Quick method. The remainder of the cellular pellet is submitted for cell block. Hematoxylin and eosin stain and appropriate immunostains for the malignancy being treated will supplement the same day cytology report several days later.Interpretation of the slides for same day cytology: A slide should be interpreted as positive if clusters of or individual cells are detected. For an experienced cytopathologist differences between cancer cells and reactive mesothelial cells should be apparent.Time allowed for the final report for the same day cytology: The primary goal of this pilot study is to demonstrate the feasibility and reproducibility of the same day cytology. To be successful the results of the cytology must be available when the cancer specimen is removed. A 3 h time allowed for the final report of the same day cytology is required. Early reporting is of benefit in that preparation for HIPEC will be facilitated.Standard HIPEC for positive same day cytology: If the same day cytology is positive a standardized HIPEC regimen is performed. The HIPEC methodology may be open or closed at the discretion of the surgical oncology team. The chemotherapy agents to be used are selected by the peritoneal surface malignancy team. The HIPEC treatment is maintained for 90 min at 42°C in the whole abdomen and pelvis.Review of slides obtained by same day cytology: All slides will be stored for consultation within a group meeting of pathologists/cytologists from all participating institutions. A record of positive cytologies by digital photography is recommended. All negative slides will be reviewed to assess the quality of the staining technology.Accrual: The plan is to continue the study until 20 positive same day cytology reports with HIPEC administered have been achieved. The total number of patients in the feasibility trial cannot be estimated at this time.Future plans: A randomized trial to test the efficacy of HIPEC in patients with positive same day cytology is planned.Ethics approval and consent to participate from patients for this study will be obtained.

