## Ethical approval and consent to participate

The phase I protocol is to be offered to a single as yet not identified institution. This institution will construct an appropriate consent with the ethics committee/institutional review board. All cytology specimens/human data will be performed in accordance with relevant guidelines and regulations.

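### Reproducibility is part of the primary goal, but the protocol specifies no assessment of agreement for the same day reading

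*Protocol article*

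**What the plan says.** All but the last of these statements stand in the Methods section of the protocol article.

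- **Goal** (item on time allowed for the final report): "The primary goal of this pilot study is to demonstrate the feasibility and reproducibility of the same day cytology".
- **Success** (same item): "To be successful the results of the cytology must be available when the cancer specimen is removed". A limit of 3 h is attached. No criterion for agreement or accuracy follows.
- **Cell block** (item on staining and reading): "The remainder of the cellular pellet is submitted for cell block". The rule is not restricted to positives or to negatives. The H&E stain and immunostains "will supplement the same day cytology report several days later".
- **Slide review:** "All slides will be stored for consultation within a group meeting of pathologists/cytologists from all participating institutions". Digital photography of positives is recommended. For negatives: "All negative slides will be reviewed to assess the quality of the staining technology".
- **Consequence and accrual:** a positive same day report leads to HIPEC, and accrual runs until 20 positive reports with HIPEC given. Total enrolment is not estimated.
- **Sites** (Ethical approval and consent to participate): "The phase I protocol is to be offered to a single as yet not identified institution".

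**The concern.** The article names two things to demonstrate, feasibility and reproducibility, and gives a measure for the first only. A report that arrives on time counts as success whether or not the call was right. Each positive call followed by HIPEC counts towards the 20, confirmed or not.

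The two sources that could show reading error are given other jobs. The negative review is aimed at stain quality, not at the diagnosis. The cell block supplements the report, and neither a comparison nor a way of handling discordant results is stated.

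Two things are at stake. A false positive reading means that HIPEC was given without the target the rationale relies on, and a false negative reading defeats the selection. The randomized trial planned next, in patients with a positive same day result, would also inherit a selection error that nobody had measured.

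**Working it through.** **1. Is there a figure to reproduce?** No. The 20 positives are a stopping count and are not derived from precision, power or an error rate. The check is therefore of goal against measure.

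| Part of the primary goal | Measure stated in the article |
|---|---|
| Feasibility | Result available when the specimen is removed; 3 h limit |
| Reproducibility | None stated |

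| Material collected | Purpose stated | Could it show reading error? |
|---|---|---|
| Cell block, H&E, immunostains | Supplement the report | Yes, if compared with the same day call |
| All slides, stored | Consultation at a group meeting | Yes, if re-read for the diagnosis |
| Negative slides, reviewed | Staining quality | Not for that purpose |
| Photographs of positives | Record, recommended only | No re-read stated |

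**2. How large might reading error be among the 20?** This is illustrative only. Sensitivity (Se) and specificity (Sp) are assumptions; the document gives neither. Positivity p comes from the Background: about 10% (endometrial cancer), 15.2% (colon cancer before resection, 125/822) and 32% as printed (gastric cancer, denominator not shown). These are observed cytology rates, used here in place of true positivity.

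False positives among 20 = 20 × (1 − p)(1 − Sp) / [p·Se + (1 − p)(1 − Sp)]

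Example with p = 0.10, Se = 0.80, Sp = 0.95: 20 × 0.045 / (0.080 + 0.045) = 7.2.

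| p (Se = 0.80) | Sp 99% | Sp 98% | Sp 95% | Sp 90% |
|---|---|---|---|---|
| 10% | 2.0 | 3.7 | 7.2 | 10.6 |
| 15.2% | 1.3 | 2.4 | 5.2 | 8.2 |
| 32% | 0.5 | 1.0 | 2.3 | 4.2 |

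**3. What would the comparison deliver?** The intervals are exact (Clopper-Pearson), two-sided 95%. With no discordant result among n, the upper limit is 1 − 0.025^(1/n).

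Positives, n = 20:

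| Discordant | 95% interval |
|---|---|
| 0 of 20 | 0 to 16.8% |
| 1 of 20 | 0.1 to 24.9% |
| 2 of 20 | 1.2 to 31.7% |
| 4 of 20 | 5.7 to 43.7% |

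Negatives: the expected total is 20/p if every positive receives HIPEC, and the negatives are that total less 20.

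| Positivity | Expected total | Negatives | Upper limit if none discordant |
|---|---|---|---|
| 10% | 20/0.10 = 200 | 180 | 2.0% |
| 15.2% | 20/0.152 ≈ 132 | 112 | 3.2% |
| 32% | 20/0.32 = 62.5 | about 42 | 8.4% |

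The error proportions can thus be estimated from planned material, well for negatives at low positivity and loosely for positives.

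**4. Number of sites.** The only possible second look is a meeting of readers from all participating institutions, while the ethics section offers the protocol to one institution. Both cannot hold. With one site, between-site reproducibility cannot be shown.

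**The case against.** **Checks exist.** A reader might infer that the same day call is never checked, that the error rates cannot be estimated, or that every false positive would stay invisible. The text does not support any of these. The rest of each pellet goes to cell block, so a discordant result could appear in the patient's supplemented report. All slides, positives included, are kept for group consultation. What is missing is a stated comparison and a diagnostic purpose for the review.

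**Reproducibility may mean reliable delivery.** The Objectives name feasibility only, the abstract describes success as coordination between departments, and reproducibility appears once, beside a timing rule. That reading is possible. Even so, the article gives no measure for it beyond timing and does not say which meaning is intended.

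**Detail belongs elsewhere.** The choice of kappa, interval method and masking may well sit in a full protocol or analysis plan. The point does not depend on them. The article itself fixes the success criterion, the purpose of the negative review and the role of the cell block, and these do not serve the stated goal.

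**The size is soft.** This stands. Accuracy is assumed, and the high counts come from low positivity.

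**The cell block is not a full reference.** This also stands. It comes from the same pellet, so it can reveal a wrong reading but not malignant cells that the lavage missed. The statement in Methods that same day cytology can reduce false negatives follows an assumption about four-site lavage versus paracentesis, and this comparison would not test it.

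**Conclusion.** The concern holds as a mismatch between goal and measure. Reproducibility is part of the primary goal, no agreement assessment is specified, and the review that is specified is aimed at staining. If the plan is followed as written, reading error will not be estimated in either group, although the material will be there.

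The extent of error is unknown. The range of roughly 0.5 to 11 false positives among 20 rests wholly on assumed sensitivity (80%) and specificity (99 to 90%) and on positivity between 10% and 32%. The conclusion does not depend on that range. The documents do not support saying that the error rates are beyond estimation, or that a comparison with the cell block would give sensitivity for peritoneal disease.

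**What to change.** 1. State what reproducibility means here, and keep the timing criterion as the measure of feasibility.
2. Pre-specify a cross-tabulation of every same day result, positive and negative, against the final cell block and immunostain diagnosis. Report the discordant proportion among positives and among negatives with exact 95% intervals.
3. State that this measures reading error within one specimen and not sampling false negatives. Do not claim that the study shows a reduction in false negatives.
4. At the group meeting, widen the review from staining quality to the diagnostic call, and include positives.
5. Reconcile the single institution in the ethics section with the several in Methods. If the study stays single-site, limit any reproducibility claim to that site.

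A masked re-read of all or a sample of slides, reported with kappa, is optional. If wanted, it should be arranged before accrual so that readers have not yet seen the cell block result.

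**Cost.** Items 1 to 3 and 5 need text and one table, since slides and cell blocks are already planned. Item 4 adds some reader time. A full masked re-read is not trivial: at four slides per patient it means about 4 × 200 = 800 slides at 10% positivity, or 4 × 63 = 252 at 32%, which is why a sample may do. The sponsor should also accept that some patients given HIPEC may prove to have had an unconfirmed reading.

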**Dissemination::**

Successful completion of these requirements is a positive result for this study and allows for future protocols to be generated. Successful completion of the same day cytology phase 1 protocol will allow the efficacy, safety, and efficiency of this plan of patient management to be evaluated.

HighlightsThe determination of positive versus negative peritoneal cytology at the time of a surgical intervention is not currently routinely performed.The methodology for making the results of peritoneal cytology available in the operating theater is not currently in use.A standardized use of hyperthermic intraperitoneal chemotherapy (HIPEC) is in patients with positive peritoneal cytology.A workable protocol to identify positive peritoneal cytology during a surgical procedure as an indication for HIPEC is a necessary first step toward improved patient care.Optimal management plans for patients found to have positive peritoneal cytology at the time of a surgical procedure need to be determined.

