• Subjects who have previously undergone intraperitoneal chemotherapy. • Subjects with preoperative or intraoperative biopsy consistent with peritoneal metastases or disseminated disease. • Other prior malignancies, except for cured non-melanoma skin cancer, curatively treated *in situ* carcinoma of the cervix, adequately treated malignancies for which there has been no evidence of activity for more than three years, or indolent tumors for which observation over 2 years is a reasonable option. • High suspicion for extra-abdominal metastases. • Women who are pregnant or lactating. • Subjects with a condition which may interfere with their ability to understand the requirements of the study. • Active coronary artery disease (defined as unstable angina or a positive cardiac stress test). Subjects with a history of coronary artery disease may be included if they have had a normal stress test within 60 days of enrollment or are determined by a cardiologist to be of acceptable perioperative risk. • Uncontrolled hypertension defined as greater than 140/90 and not cleared for surgery at the time of consent. • New York Heart Association (NYHA) Class II or higher congestive heart failure; restrictive or obstructive pulmonary disease that would limit study compliance or place the patient at unacceptable risk for participation in the study. • History of cerebrovascular disease that would limit study compliance or place the patient at unacceptable risk for participation in the study. • Subjects with other concurrent severe medical problems unrelated to the malignancy that would significantly limit full compliance with the study or place them at unacceptable risk for participation in the study. • Patients with known cisplatin, carboplatin, or pemetrexed allergy. • Evidence of extensive intraperitoneal adhesions at the time of surgery, which prohibits intraperitoneal therapy, as determined by the operating surgeon. • Any condition that would preclude the ability to deliver appropriate intraperitoneal chemotherapy. • Use of an oral medication, lacking a suitable nonoral substitute, that if held for up to 10 days would be felt an unacceptable risk by the investigator. • Life expectancy less than 12 weeks.

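### Accrual stops on a count of positives who received HIPEC, with no maximum sample size and no proportion below which the strategy is declared not feasible, so reaching 20 does not by itself demonstrate feasibility

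*Protocol article*

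**What the plan says.** The Objectives section of the protocol article sets the goal as showing that same day cytology can feasibly select completely resected patients for HIPEC. The Methods section, under the time allowed for the final report, narrows this: "The primary goal of this pilot study is to demonstrate the feasibility and reproducibility of the same day cytology". It then gives a condition for each patient: "To be successful the results of the cytology must be available when the cancer specimen is removed", and "A 3 h time allowed for the final report of the same day cytology is required". No proportion of patients is attached to either.

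Under Accrual, the same section says: "The plan is to continue the study until 20 positive same day cytology reports with HIPEC administered have been achieved". The next sentence is: "The total number of patients in the feasibility trial cannot be estimated at this time".

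The Dissemination paragraph of the abstract says: "Successful completion of these requirements is a positive result for this study". The Goals section makes HIPEC conditional on a complete resection as well as a positive report.

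Two exclusion criteria in Table 2 bear on who can receive HIPEC. One operates during surgery: "Evidence of extensive intraperitoneal adhesions at the time of surgery, which prohibits intraperitoneal therapy, as determined by the operating surgeon". The other can do so: "Any condition that would preclude the ability to deliver appropriate intraperitoneal chemotherapy".

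**The concern.** A feasibility study asks how often a pathway works. The accrual rule counts only patients in whom two steps both happened: a positive same day report, and HIPEC given. A positive patient who did not receive HIPEC does not advance the count, and recruitment continues. With no ceiling and no failure proportion, the time at which the study stops and the count at which it stops say little about how well the pathway performs.

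The article plans a randomised trial as the next step. If reaching the accrual target were taken as the evidence for going ahead, a poorly working pathway would pass on the same count as a good one.

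**Working it through.** **The planned figure.** The 20 comes with no rate, error level, power or precision, so there is no calculation to reproduce. The rule is inverse (negative binomial) sampling with r = 20.

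**Step 1: positives needed to reach 20.** Let d be the share of positives who receive HIPEC. The article gives no value, so the values below are assumptions. Expected positives = 20/d, with the 5th to 95th percentile range from the negative binomial distribution.

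| Assumed d | Expected positives | 5–95% range | Expected without HIPEC |
|---|---|---|---|
| 90% | 20/0.9 = 22.2 | 20–25 | 2.2 |
| 50% | 20/0.5 = 40 | 31–51 | 20 |
| 30% | 20/0.3 = 66.7 | 48–89 | 46.7 |

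With no cap, the probability of eventually reaching 20 is 1 for any d above zero. This assumes unlimited time and resources.

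**Step 2: what the count leaves open.** The same 20 HIPEC treatments support very different delivery rates, depending on how many positives there were. Clopper–Pearson 95% limits (nominal, because the number of positives is itself random under this rule):

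| HIPEC / positives | 95% CI |
|---|---|
| 20/20 | 83–100% |
| 20/25 | 59–93% |
| 20/40 | 34–66% |
| 20/67 | 19–42% |

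The information is therefore available if all positives are reported. It lies in the denominator, for which the article sets neither a ceiling nor a bar.

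**Step 3: can total N be bounded?** Expected N = 20/p, where p is the positivity rate and every positive counts towards the 20. The rates are those in the article's background sections.

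| Source in the article | p | 20/p | 5–95% range |
|---|---|---|---|
| Gastric, as printed | 32% | 62.5 | 45–83 |
| Colon, before resection (125/822) | 15.2% | 132 | 91–179 |
| Colon, after resection (64/533) | 12% | 167 | 114–228 |
| Endometrial, confined to uterus | about 10% | 200 | 136–275 |
| Uterine sarcoma (146/1481) | 9.9% | 202 | 137–278 |
| Gastric, 93 of the 1241 named | 7.5% | 267 | 180–368 |

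The two gastric rows differ because the printed 32% does not match 93 of 1241 and its base is not given. A planning range of about 60 to 270 follows. If only half of the positives counted (an assumption), the means would double, to about 125 to 534.

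**Step 4: would a fixed denominator discriminate?** Take 20 positives counted whatever followed, with an illustrative bar of at least 16 given HIPEC. From the binomial distribution, P(X ≥ 16) is 0.957 at a true rate of 90%, 0.630 at 80%, 0.051 at 60% and 0.006 at 50%. The bar is an assumption, used only to show that such a rule can fail a weak pathway.

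**The case against.** The strongest defence is that inverse sampling is a legitimate design. Nothing in the article says that positives without HIPEC will be discarded, so 30% delivery would end near 20 of 67 and be visibly different from 20 of 21 or 22. That stands. A reader might infer that every such trial ends with 20 of 20; the text does not support this, because the rule fixes a numerator and not a result.

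Other tempting readings also go too far:

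- **That late positives do not count.** The accrual sentence has no time condition. A positive same day report that took more than 3 h but was followed by HIPEC would satisfy it.
- **That the abstract makes reaching 20 the positive result.** The requirements it refers to are the steps in the paragraph before it: coordination of services, consent, collection, preparation, reading and timely reporting.
- **That incomplete resection is a hidden pathway failure.** Complete resection is a condition for HIPEC by design.
- **That the intraoperative exclusions remove patients from the denominator.** Table 2 governs eligibility. No section says how such patients are reported, so this calls for clear reporting and is not evidence of a flaw.

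It is also fair that timely reporting, the stated primary goal, can be observed in every patient with a specimen, including those with negative cytology. The HIPEC-based count does not hide it.

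Finally, a full protocol or analysis plan may define the rates and intervals, and the case mix is unknown while the institution is unidentified. This explains the lack of a single total N. It does not remove the point, because the stopping rule is fixed in this text and an analysis definition would not change when accrual stops. The article's own rates are enough to set a ceiling.

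**Conclusion.** The point holds in this form: accrual stops on HIPEC-treated positives, no maximum is set, and neither timely reporting nor HIPEC delivery has a proportion below which the strategy would be called not feasible. The target is met at any non-zero delivery rate, after about 22, 40 or 67 positives at 90%, 50% or 30%. Meeting it is therefore not a demonstration of feasibility.

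It does not follow that the trial is uninformative. Both rates can be estimated if all patients are reported. What is missing is a rule that could turn those estimates into a negative conclusion. Recruitment might stall in practice, but the article does not define that as a result.

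The delivery rates and the 16 of 20 bar are assumptions. The range of 60 to 270 rests on the article's mixed-tumour positivity rates and on every positive counting.

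**What to change.** Change the accrual paragraph and add a decision rule:

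1. Stop at 20 consecutive positive same day reports in patients with complete resection, whether or not HIPEC followed, or at a stated maximum number of patients with a collected specimen, whichever comes first. Choose the maximum from the 60 to 270 range once the case mix is known.
2. Report timely reporting as on-time results over all patients with a collected specimen.
3. Report delivery as HIPEC given over all cytology-positive, completely resected patients.
4. Give each proportion an exact 95% CI and a minimum value, fixed before the first patient, below which the strategy is declared not feasible. State the delivery minimum so that it also applies if the maximum is reached with fewer than 20 positives.
5. Report patients excluded during surgery, with reasons.

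One denominator belongs to each rate. The delivery denominator is 20 unless the cap intervenes. The timeliness denominator stays random but is bounded by the cap.

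The cost is wording only, since the article says the institution is not yet identified. The downsides are that fewer than 20 HIPEC treatments may be observed and that the trial can return a negative result.
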